### 2.4. Randomisation and Blinding

Participants meeting the predetermined inclusion criteria will be randomly allocated to the BFR group (n = 24) or the sham BFR group (n = 24). For the randomisation of the participants, the “block randomisation” method will be applied through the randomisation website (http://www.randomization.com) by an external researcher, who will not have any contact with the participants throughout the study [27,36]. To ensure a balance in sample size between groups over time, we will randomise participants using a block randomisation method (blocks of 4). Random codes will be sealed in opaque envelopes and delivered to the physical therapist, who will undertake the intervention by an administrative assistant who will not be involved in the study [26].

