## 2. Materials and Methods

### 2.1. Study Design

This crossover design randomised controlled clinical trial will include two intervention arms (BFR and sham BFR) with three assessment time points (baseline, immediately after BFR training, and at the end of the shoulder girdle exercise loading session) (Figure 1). Outcome measures assessment during the first (DAY 1) and the second session (DAY 2) will be performed by a blinded independent assessor to the intervention (sham BFR or BFR) to avoid the risk of “data collection ascertainment bias”.

All participants will be blinded to the group allocation to avoid the risk of “expectation bias” and “patient ascertainment bias” [27]. To achieve this, they will be informed that the effect of two different BFR occlusion protocols on pain perception after a low-load resistance exercise bout will be evaluated. The physiotherapists performing the interventions (BFR or Sham BFR) will not be blinded; however, they will not participate in the outcome assessment and will be blinded to the recorded values.

All participants will have an introductory baseline assessment. They will be asked to fill out questionnaires on sociodemographic characteristics, symptoms, comorbidities, and functional limitations. Subsequently, measurement of pain pressure thresholds (PPTs), administration of the Shoulder Pain and Disability Index (SPADI), measurement of maximal voluntary isometric contraction (MVIC), assessment of pain during active abduction, and maximal pain in shoulder external rotation on the numeric pain rating scale (NPRS) will be recorded. Then, participants will be randomly allocated to one of the two intervention groups (BFR and Sham BFR) and will be asked to perform one exercise with BFR. Immediately after the BFR session, they will be asked to evaluate the level of difficulty or exertion experienced during the BFR or Sham BFR exercise using the Borg CR1O scale [28]. Simultaneously, measurement of PPTs, MVIC, and maximal pain during external rotation, pain during active shoulder abduction, and perception of improvement or worsening of symptoms will be recorded. Finally, the participants will be asked to perform the shoulder girdle loading protocol, and a final assessment of the same outcome measures will be performed.

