The primary outcome used to calculate the required sample size using G* Power (v 3.1) software was pain. The sample size calculation was based on a previous study that reported an effect size of d = 0.6 for differences in the NPRS between groups after the BFR exercise [26]. To achieve 95% power at an alpha level of 0.05, 20 patients per intervention for 3 assessment periods of outcome measures are required. Given the crossover design of the study and the possibility that the status of the participants will change between the first and the second intervention, it is estimated that there will be a dropout of 20%, and thus, it is proposed to recruit 24 participants per group into the study, or 48 participants in total.

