## 3. Discussion

Nonspecific shoulder pain, as mentioned above, brings about a substantial economic impact not only on the national health systems but also on the patients themselves, leading them to pain chronicity, increasing in parallel the risk of adverse consequences such as decreased participation and quality of life, absenteeism at work, and early retirement [1,2,3,61]. Consistent with the available literature, a rehabilitative program that includes strengthening exercises for the scapula and rotator cuff muscles appears beneficial for improving individuals’ function and quality of life with nonspecific shoulder pain [12,62,63,64]. Despite this, up to 30% of individuals still present with pain and disability after rehabilitation interventions due to the continuation of the pain, which leads to dissatisfaction and difficulty in completing such exercise programs [61]. Thus, we aim to investigate whether a single BFR training session with a low load may be used to reduce pain and provide a window of opportunity for clinicians to optimally load otherwise painful tissues and joints.

The specific type of study was chosen since it was considered the most appropriate to examine any direct acute effect with regard to pain perception following BFR training, since the result of the intervention is compared within the same participant, and each participant serves as his own control without ethical issues arising from a placebo group. Another advantage of this design is the reduction of inter-participant variability by comparing the two interventions. Finally, the crossover design provides higher statistical power, even with a smaller number of participants, than simple randomised controlled clinical trials [65].

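### The single published block size of 4, with envelopes going to the unblinded treating therapist, makes about a third of the treatment orders predictable; the exposure is limited to comparisons between sequence groups

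*Protocol article*

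**What the plan says.** Section 2.4 has participants "randomly allocated to the BFR group (n = 24) or the sham BFR group (n = 24"). It gives one block size, "we will randomise participants using a block randomisation method (blocks of 4"), and the reason offered is balance in group size over time. The list is made "by an external researcher, who will not have any contact with the participants throughout the study". On handling, it says "Random codes will be sealed in opaque envelopes and delivered to the physical therapist, who will undertake the intervention", with an uninvolved administrative assistant making the delivery.

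Section 2.1 states that "The physiotherapists performing the interventions (BFR or Sham BFR) will not be blinded", but adds that "they will not participate in the outcome assessment and will be blinded to the recorded values". Participants and the outcome assessor are blinded, and allocation follows the baseline measurements. Section 2.6 places data collection at one university site. No stratification factor is stated anywhere.

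The trial is a crossover, so the randomised quantity is the order of the two conditions. The Discussion notes that "each participant serves as his own control".

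**The concern.** With one list, equal allocation and a known fixed block of 4, each block holds exactly two of each order. Once two of the same order have been seen in a block, the rest of that block is known, and the fourth assignment is always known. Sealed opaque envelopes do not prevent this, because the prediction comes from past allocations and not from opening anything early. The unblinded therapist sees the condition given on DAY 1 and so is well placed to keep count.

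If such knowledge influenced who was entered next, the BFR-first and sham-first groups could differ systematically. Three things rest on comparing those groups:

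- the DAY 1 comparison of BFR with sham;
- the day-by-treatment interaction, which section 2.7 includes among all interactions. In a two-period, two-sequence design it coincides with the sequence difference and serves as a statistical check on carryover;
- DAY 1-only data from participants who do not complete session 2 (section 2.3 anticipates 20% dropout). A model with participant random effects uses these data as between-person information.

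The stated benefit of the small block is modest here. Both conditions are given to everyone and the model already contains a day effect, so close balance over calendar time matters less than in a parallel-group trial.

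**Working it through.** **Inputs.** Block size 4 and two groups of 24 (section 2.4); 48 participants in total (section 2.3: "it is proposed to recruit 24 participants per group into the study, or 48 participants in total"); one site (section 2.6); no strata stated.

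**The plan's own figure.** 48 / 4 = 12 complete blocks, each with 2 of each order. 12 × 2 = 24 per group, so 24:24 reproduces.

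**Certain assignments.** An assignment is certain when one order's quota in the block is already used up. A block of 4 has six equally likely arrangements:

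- AABB and BBAA: positions 3 and 4 are certain, so 2 each.
- ABAB, ABBA, BAAB and BABA: only position 4 is certain, so 1 each.

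Mean per block = (2 × 2 + 4 × 1) / 6 = 8/6 = 4/3, which is 33.3% of 4. Over 12 blocks: 12 × 4/3 = 16 of 48. The minimum is 12 × 1 = 12 (25%) and the maximum 12 × 2 = 24 (50%). The variance per block is 1/3 × 2/3 = 2/9, so the SD over 12 blocks is √(12 × 2/9) = 1.6. A simulation of 48 allocations gave 16.02.

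**Correct guesses, always choosing the less-used order.** Probability of being right by position:

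- position 1: 1/2
- position 2: 2/3
- position 3: 1/3 × 1 + 2/3 × 1/2 = 2/3
- position 4: 1

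Sum = 17/6 per block. (17/6) / 4 = 70.8%, or 12 × 17/6 = 34 of 48, against 50% by chance.

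**Alternatives.** The documents name none, so these are illustrative. Fixed blocks are exact; varied blocks and the single list are simulated. For varied blocks, the count of certain assignments assumes that the observer knows the possible sizes but not their order.

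| Scheme | Certain, of 48 | Guessed right |
|---|---|---|
| Fixed 4 (the plan) | 16 (33.3%) | 70.8% |
| Fixed 6, known | 12 (25%) | 68.3% |
| Fixed 8, known | 9.6 (20%) | 66.6% |
| Varied 4, 6 | 2.7 (5.7%) | not calculated |
| Varied 4, 6, 8 | 1.1 (2.3%) | 67.7% |
| One permuted 24:24 list | 1.9 (4%) | 58.0% |

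Varying the size removes nearly all certainty but little of the advantage in guessing. A single list reduces both.

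**The case against.** The strongest reply is that the main comparison is hardly touched. Only order is randomised, everyone is meant to receive both conditions, and each session has its own pre-treatment baseline. If staff did shift the kind of participant entered, a stable difference in level would already be present at that session's baseline and would cancel in the treatment-by-time contrast, even for participants with DAY 1 data only. Distorting that contrast would require selection on responsiveness to BFR, and nothing in the text suggests this. The objection stands and is why the point ranks low.

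The mechanism is also not established. The article does not say that the therapist screens or enrols, eligibility rests mostly on listed criteria, and outcomes are taken by a blinded assessor. Certainty requires knowledge of every earlier allocation and of the block boundaries. Section 2.1 speaks of physiotherapists in the plural, so several therapists would have to pool what they know. These conditions also stand.

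The day-by-treatment term is not the only safeguard against carryover. Section 2.1 asks about changed clinical status before session 2 and excludes those who report a change.

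A reader might go further and infer that the BFR effect itself is biased, or assume some shift in the participants entered and set the result against the d = 0.6 in section 2.3. The documents support neither. They give no figure for such a shift, and a difference in level between sequence groups on DAY 1 is not a shift in the within-person treatment effect.

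What the objection does not remove is that the fixed, published block and the unblinded recipient of the envelopes are stated design choices, and the predictability follows from them.

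**Conclusion.** The point holds as a minor weakness in allocation concealment. Under the stated scheme, an observer who has all earlier allocations would know an expected 16 of 48 orders in advance (range 12 to 24) and could guess 34 of 48 correctly. One third is an average that depends on that knowledge; it is not a claim that a third of allocations will in fact be known.

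The within-person contrast in completers is largely protected. The exposure is confined to comparisons between the two sequence groups. Its size cannot be derived from the documents, and it is nil if foreknowledge does not influence entry. The change is worth making because it is nearly free, not because the main result is in danger.

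**What to change.** In section 2.4, replace the fixed block of 4 with randomly varied block sizes (for example 4, 6 and 8), generated by the same external researcher, and state that the sizes are not disclosed to therapists or assessors. Certain assignments then fall from 16 to about 1 to 3 of 48, depending on the sizes chosen. Correct guessing falls only to about 68%.

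If balance over calendar time is judged unnecessary in this crossover, a single permuted list of 24 BFR-first and 24 sham-first is an option. It leaves about 2 of 48 certain and 58% guessed right, but gives up the purpose for which section 2.4 chose blocking, so it is a matter of judgement.

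The cost is one new list and a sentence of protocol text, with no extra participants or staff. The small downside is slightly looser balance of the two sequences over time, or if recruitment stops early.

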### 2.5. Interventions

Prior to the main part of the intervention, all patients will be familiarised with the exercise protocol. The only difference between the two intervention groups will be the percentage of BFR cuff pressure. The total duration of the two interventions, including the measurements, will be approximately 1 h.

#### 2.5.1. Sham Group

In the sham BFR group, the cuff will be placed firmly around the proximal deltoid and automatically inflated until there is enough room for two fingers between the skin and the cuff. This will be automatically applied via the MAD-UP^®^ system, which has been designed based on published research and does not promote tissue adaptation (i.e., neurological, structural) [37].

#### 2.5.2. BFR Protocol

The vascular occlusion pressure needed for the complete occlusion of the upper extremity blood flow will be measured at rest, with the participant relaxed in the standing position [38], by placing a 6 cm wide and 60 cm long cuff on the more proximal part of the affected upper limb using an automatic personalised tourniquet system designed to automatically calculate limb occlusion pressure (MAD-UP Pro system, Angers, France) with clinically acceptable accuracy and high reliability [39,40]. Both intervention groups will perform the same exercise protocol. The limb occlusion pressure will be set at 50–60% of the complete occlusion pressure for the intervention group [35].

#### 2.5.3. Exercise Protocol

All participants will perform biceps curls with a dumbbell from a standing position using BFR or sham BFR. The rhythm of the exercise will be paced using a metronome (60 bpm), and the biceps curls for each muscle contraction mode (concentric or eccentric) will last 2 s [41]. The initial resistance load will correspond to 5% of each participant’s body weight (±0.250 kg). Participants will be asked to perform 4 sets of bicep curls. The first set will consist of repetitions until failure (inability to follow the pace of the metronome, inability to complete the contraction on full range, or inability to perform an additional contraction), followed by 3 sets of 15 repetitions with a 30 s rest between the sets while the cuff remains inflated [25]. Therapists will encourage the participants to reach their maximum possible number of repetitions and inform them of the importance of completing all four sets. The participants’ inability to complete all set repetitions or to follow the pace of the metronome will indicate a resistance load reduction of 0.5 kg [42]. Immediately after the execution of the biceps curl exercise, the cuff will be deflated and removed for both groups.

#### 2.5.4. Muscle Loading Protocol of the Shoulder Girdle after the BFR Application

Five minutes after the execution of the biceps curl exercise, each participant will receive a structured physiotherapy session consisting of six therapeutic exercises targeting the rotator cuff and scapula muscles. Initially, the participants will be asked to perform two warm-up exercises that activate several muscle groups of the shoulder girdle: (1) a bear hug exercise from a standing position using a pulley, and (2) a low row exercise using a pulley [43] (Supplementary File S1). Both exercises will be performed in 4 sets of 12 repetitions at a ratio of 2 s concentric to 2 s eccentric contraction paced using a metronome. Calculation of the load will be performed using the 2 in-reserve method [22]. Then, the participants will proceed to the main part of the training, which will include the following exercises: (1) shoulder press (closed grip) from a seated position, (2) internal rotation of the shoulder, (3) external rotation of the shoulder with a towel under the armpit (20 o–30 o relative shoulder abduction position), and (4) shoulder flexion. Apart from the shoulder press exercise, the other three exercises will be performed in the standing position [44,45] (Supplementary File S1). A modified pain monitoring approach will dictate the loading, so the patient will report a maximum of 4/10 during familiarisation or training [26,42,44,45]. The participants will start with the shoulder press exercise, performing four sets with a load corresponding to 10% of their body weight. All four sets will be performed until failure, with a one-minute rest between sets [26,42]. For the remaining exercises, the load will be set at 5% of their body weight. Likewise, all four sets will be performed until failure, with a one-minute rest between sets. The physiotherapy session will be performed without the use of BFR.

### 2.6. Data Collection

Data collection will take place on the premises of the European University Cyprus before the beginning of the interventions (baseline), immediately after the biceps curl exercise with BFR and sham BFR (pre-loading), and after the end of the shoulder girdle training session (post-loading). Then, the participants will undergo a 72-h wash-out period to avoid any potential carryover effects before the intervention crossing over.

The main outcome measures will be: (a) identification of PPTs (three local and three remote sites), (b) maximal pain during MVIC of shoulder external rotators, and (c) MVIC of shoulder external rotators.

#### 2.6.1. Pressure Pain Threshold Assessment

PPTs will be assessed using a handheld mechanical pressure algometer (Wagner Instruments, Riverside, CT, USA) with a 1 cm^2^ rubber disk attached to the pressure gauge by applying the probe perpendicularly to the skin at a pressure rate increase of approximately 1 kgf per second. One assessor blinded to the group allocation will obtain PPT measurements with the participants in long sitting with both arms resting on the plinth. The participants will be instructed to report the moment when the pressure sensation changes into slightly unpleasant pain. PPT assessment sites will be located, marked, and evaluated over (1) the upper trapezius (middle of the distance between the acromion and spinous process A7), (2) the supraspinatus (muscle belly muscle just below the middle of the spine of the scapula), (3) the middle deltoid (middle distance from the acromion and the epiphysis of the muscle), (4) the abductor pollicis longus (midway of muscle belly), (5) the quadriceps (midway between anterior superior iliac crest and superior pole of patella), and (6) the tibialis anterior muscle (muscle belly, midway between tibial tuberosity and ankle) [23,46,47,48]. The average pressure, in kilograms, of the three trials will be used for data analysis. The order of scoring points will be randomised between patients with 30 s intervals between the three trials. PPT assessment using a handheld algometer has been reported to be a valid and reliable procedure [49,50,51].

#### 2.6.2. Maximal Pain and Strength in Isometric Shoulder External Rotation

The MVIC of shoulder external rotation will be assessed using a handheld dynamometer (Kinvent, Montpellier, France) from a standing position, with the legs apart at shoulder height, the hips and knees in slight flexion, and the elbow on the examined upper limb at 90° flexion with the thumb facing up. A towel will be placed at the height of the elbow to slightly abduct the shoulder at 20–30° [52].

The participants will be asked to apply a progressive MVIC of the external rotators for 5 s, instructing them to “push, push…push…push…push…relax” in a monotone voice [53]. If the participant cannot exert more force due to pain, the MVIC will be calculated until that point. The examiner will hold the handheld dynamometer in a position to achieve perpendicular alignment with the styloid process of the ulna [52]. The handheld dynamometer has demonstrated perfect test-retest reliability with an interclass correlation coefficient (ICC) of 0.92–0.98 and very good to perfect inter-examiner reliability with an ICC of 0.84–0.96 for assessing the MVIC of shoulder external rotation [52,54]. The maximum value from three successful trials separated by a minimum 30-s break (trials with more than 15% difference will be discarded) will be used for the statistical analysis [52]. In addition, during the test, the participants will be asked to rate their pain based on the NPRS (0–10).

#### 2.6.3. Secondary Outcomes

The following secondary outcomes will also be assessed: (a) pain during active shoulder abduction (0 to 180°) in the standing position using the NPRS, (b) patient-perceived pain change using a global rating of change scale (GROC) based on a 7-point Likert scale ranging from “Much better—a very important improvement” to “Much worse—an important aggravation” [55] (not applicable at baseline), and (c) the participants’ rating of perceived exertion (RPE) using a modified Borg’s scale (Borg CR10) immediately following the BFR or sham BFR exercise session. The scale has been shown to be a valid alternate tool for estimating exertion and intensity levels during resistance training [56]. A printed version of the modified scale will be presented to the participants, and it will be explained to them that a very hard session would have a rating of ≥7 out of 10 and a rating of 10 means that they were giving maximal effort and could not exert themselves any further. Accordingly, a light session may have a rating of Borg ≤ 2, a moderate session may have a rating of Borg >2–<5, and a hard session may have a rating of Borg ≥5–<7. (d) The Shoulder Pain and Disability Index (SPADI) questionnaire assesses the pain and difficulty experienced by the participant in daily activities of the upper extremity [57]. This questionnaire consists of two parts. During the first part, the participants will be evaluated on a scale of 0–10 on the pain they experience in daily activities, and during the second part, the participants will be evaluated on the difficulty they experience in performing the various daily activities (0–10). This questionnaire has been translated and cross-culturally adapted for the Greek-speaking population [58].

### 2.7. Statistical Analysis

Descriptive statistics will be used to present and describe participant characteristics (values will be presented as mean and standard deviation or median and interquartile range).

The residuals of each variable/model will be tested for normality by visual inspection of frequency histograms and Q–Q plots [59] or by using the Shapiro–Wilk test [60]. Mixed-effects models will be constructed considering the primary outcome measures (PPTs, MVIC, and maximal pain during external rotation) using participant random effects for all assessment time points. Fixed effects will include the day of assessment (DAY 1 or DAY 2), the two treatment groups (BFR and sham BFR), the time points of assessment of the outcome measures, and all interactions. Additionally, we will model parameter estimates for variables associated with pain responses, such as age, height, and condition chronicity. If a statistically significant effect or interaction is found, we will perform a post hoc test using Tukey’s adjustment for multiple comparisons. Statistical analyses will be conducted using JMP (v.16.0, SAS Corporation, Cary, NC, USA), and the statistical significance will be set at α = 0.05.

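### The trial is sized on one primary outcome (pain on the NPRS), but three measures, one of them PPT at six sites, are declared primary at alpha 0.05 with no error control across them

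*Protocol article*

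**What the plan says.** Three sections of the protocol article bear on what is primary.

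- **2.3 Participants and Sample Size** uses the singular: "The primary outcome used to calculate the required sample size using G* Power (v 3.1) software was pain". The calculation takes a previous study that "reported an effect size of d = 0.6 for differences in the NPRS between groups after the BFR exercise". It does not say which NPRS score is meant. Section 2.6.2 has one, taken during the external-rotation test. Section 2.6.3 has another, taken during active abduction and classed as secondary.
- **2.6 Data Collection** lists three main outcome measures. The first two are "a) identification of PPTs (three local and three remote sites), (b) maximal pain during MVIC of shoulder external rotators". The third is the strength value from that test, the MVIC itself.
- **2.7 Statistical Analysis** calls the same three primary: mixed models are built "considering the primary outcome measures (PPTs, MVIC, and maximal pain during external rotation". Significance is set at 0.05. Tukey's adjustment follows once an effect or interaction within a model is significant. Nothing is said about error control across outcomes.

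Section 2.6.1 averages the three trials at a PPT site. It does not pool across sites, and the fixed effects listed in 2.7 contain no site term.

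**The concern.** One section says the trial has one primary outcome and another says it has at least three. Which outcome is primary is a protocol decision, and here the protocol has made it in two ways that do not agree. It has also fixed the alpha and the adjustment, so this is not a detail simply left open for a later analysis plan.

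As written, a significant result at one PPT site, or on MVIC alone, could be reported as a positive primary finding while the NPRS outcome on which the trial was sized shows nothing. The hypothesis in the Introduction is about reduced pain perception, and MVIC is a strength measure. Without a rule for what counts as success, that hypothesis has no test with a controlled error rate.

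**Working it through.** **1. The plan's own sample size.** Inputs from 2.3: d = 0.6, 95% power, alpha 0.05, 20 per intervention. Assume a two-sided paired t test with d as the standardised within-person difference (dz). Power is the noncentral-t probability beyond the critical value, with noncentrality dz × √n.

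- n = 39 gives 95.5%.
- n = 40 (2 × 20) gives 95.9%.

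The stated figure is reproduced within one or two patients for **one** outcome at 0.05. The sample size is therefore not at fault here, but it allows for one test only.

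**2. Number of primary variables.** Six PPT sites + maximal pain + MVIC = 8 if each site is modelled separately. If the PPTs are pooled into one variable, the count is 1 + 1 + 1 = 3.

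**3. Familywise error if independent.** One two-sided BFR-sham test per variable at 0.05, with any significant result counted as success:

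- 8 variables: 1 − 0.95^8 = 1 − 0.663 = 0.337
- 3 variables: 1 − 0.95^3 = 1 − 0.857 = 0.143

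**4. Familywise error if correlated.** The documents give no correlations, so a common correlation is assumed and varied. The error is the probability that at least one of k equicorrelated standard normal statistics exceeds 1.96 in absolute value.

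| Common correlation | 8 variables | 3 variables |
|---|---|---|
| 0 | 33.7% | 14.3% |
| 0.5 | 25.0% | 12.5% |
| 0.7 | 19.1% | 10.9% |
| 0.9 | 11.9% | 8.4% |

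If only the six PPT sites are correlated with each other, the eight-variable figure is 28.4% at 0.5 and 24.6% at 0.7.

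**5. What Tukey covers.** It adjusts comparisons among the levels of an effect inside one model. The models for different outcomes are separate, so it does not change the figures in steps 3 and 4.

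**6. Power if the primaries are kept and alpha is shared.** Paired t, dz = 0.6, 40 completers:

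- alpha 0.05: 95.9%
- alpha 0.05/3 = 0.0167: 89.6%
- alpha 0.05/8 = 0.00625: 81.0%

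These apply to any one outcome with dz = 0.6, at the strictest step of Holm. The documents give no effect size for PPT or MVIC.

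**The case against.** - **Eight primary variables are not stated.** Sections 2.6 and 2.7 each list three measures, and how the sites are handled could be left to a fuller document. This stands in part. Separate site models are the natural reading, because no pooling and no site term are given, but they are an inference. The three-variable column is therefore a real alternative, and it still exceeds 5%.
- **Section 2.3 may only say which primary outcome was used for sizing.** Maximal pain is among the three in 2.7, so the powered outcome is still primary. This is fair. A reader might infer that the powered outcome has been displaced. The documents do not show that. They show that no rule says which outcome decides.
- **The percentages overstate the risk of a false claim that BFR reduces pain.** They count errors in both directions and include MVIC. Restricted to the seven pain variables and the direction favouring BFR, the risk is about 16% if independent, 11% at correlation 0.5 and 9% at 0.7, against a nominal 2.5%. This stands as a point of interpretation. The inflation remains.
- **A stronger figure is tempting.** Two post-treatment assessments on eight variables make 16 tests, and 1 − 0.95^16 = 56%. The documents do not support this: those two contrasts lie within one model, where 2.7 applies Tukey, so they cannot be counted as two unadjusted tests.

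**Conclusion.** The concern holds. Section 2.3 works from one primary outcome, 2.6 and 2.7 from three measures covering up to eight variables, and nothing controls the error across them. The familywise error is about 34% to 12% with eight variables and about 14% to 8% with three, over common correlations from 0 to 0.9. This rests on one BFR-sham test per variable, any single success being enough, and assumed correlations.

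A reader might take 25–34% as the trial's error rate. That range needs separate PPT models and a correlation of no more than 0.5, neither of which the documents state. What can be said without those assumptions is that every reading computed lies above 5%.

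**What to change.** Amend 2.6 and 2.7, dated before any treatment comparison is seen.

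**Preferred.** Name maximal NPRS pain during external-rotation MVIC as the single primary outcome. Test the BFR-sham contrast immediately after BFR first, at 0.05. If it is significant, test the post-loading contrast next, also at 0.05. The fixed sequence holds the error at 5% and keeps both parts of the primary objective in the Introduction (the immediate effect and its persistence after loading). The choice is consistent with the NPRS sizing, but 2.3 names neither this score nor this time point, so it should be made to do so. Move MVIC and the PPTs to secondary, with the PPTs as one local and one remote mean or as six sites, and apply Holm across them.

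**Alternative.** Keep all the primary measures, state how the PPT sites are combined, apply Holm across them, and restate the power in 2.3: about 90% at 0.05/3 or 81% at 0.05/8, instead of 96%, for dz = 0.6 and 40 completers.

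**Cost.** No new data are needed, and the preferred option needs no more participants. The protocol and the registry entry both need an amendment. Under the preferred option, PPT or MVIC alone can no longer carry the primary claim. Under the alternative, the trial accepts lower power or recruits more.
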